### Sample size

We will randomise a maximum of 1064 participants (approximately 335 Northeast London; 224 for Manchester, East London and Glasgow; and 111 for Oxford); a total study sample of 1118 participants including the 54 participants allocated to BrighterSide arm. We power for an expected difference in proportion of admission rates between arms of 7.5%, and an expected admission rate within 6 months in the TAU group of 15% (based on extensive audit data from our NHS Trusts). The design follows the methods outlined for MAMS designs with binary outcomes [29] calculated using nstagebin in Stata. It uses the same outcome at both stages and has a primary endpoint of 6 months after recruitment in each stage and the loss to follow-up rate is 5%. One-sided significance levels of 30% and 2.5% and powers of 92% and 90% are used in the 1st and 2nd stages respectively. The total sample size of 1064 represents the maximum possible sample size under the 2-stage MAMS trial design: the minimum sample size if both arms are dropped for futility at the interim analysis would be 684. The interim analysis will take place after 385 participants provide 6-month outcome data, which will occur in May 2024. The interim analysis may result in one or both interventions being removed from the trial at stage 1 (power = 92%, one-sided alpha = 0.3). The final analysis has 90% power and a one-sided alpha = 0.025. The overall family-wise error rate (FWER) is 0.0397. There is no need to account for multiple testing in a multi-arm trial with independent comparators [43]. We have allowed for a 5% missing data in the primary outcome (this is routinely available in electronic medical records, so we should have less than 5% attrition which are likely to be withdrawals).

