## Assignment of interventions: allocation

### Sequence generation

Randomisation (at the individual level) is independent and concealed using randomised-permuted blocks of random size administered by the King’s Clinical Trials Unit (KCTU; UK Clinical Research Collaboration registration 053) and which are not known to the study team. Randomisation is stratified by site. We use a 2:2:3 allocation in favour of TAU. In stage 2, we will keep the existing allocation or switch to 1:1 allocation if there is only one active intervention arm.

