## Statistical methods

### Statistical methods for primary and secondary outcomes

A detailed statistical analysis plan will be prepared and approved by the Trial Management Group (TMG), Data Monitoring Committee (DMC) and TSC prior to the interim analysis.

Descriptive statistics within each randomised group will be presented for baseline values. These will include counts and percentages for binary and categorical variables, and means and standard deviations, or medians with lower and upper quartiles, for continuous variables, along with minimum and maximum values and counts of missing values. There will be no tests of statistical significance or confidence intervals for differences between randomised groups on any baseline variable.

For the analysis of the primary outcome at both stages, we will use a generalised linear model that includes fixed effects for treatment, diagnosis and site using maximum likelihood estimation. For each pairwise comparison with TAU, we will report the difference in proportion of admissions as the estimate of treatment effect with 2-sided 95% confidence intervals and 1-sided *p* values.

Secondary outcomes with repeated measures at 3 and 6 months will be analysed at stage 2 only. These will be analysed with generalised linear mixed models (GLMMs) appropriate for the distribution of the outcome using maximum likelihood estimation. Fixed effects will be treatment, diagnosis, site, time and time*group interactions, with a random effect for participant. Treatment effect estimates will be reported as adjusted between-group mean differences in outcomes between the groups separately at 3 and 6 months with 2-sided 95% confidence intervals and 1-sided *p* values.

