### Interim analyses

For stage 1 interim analysis, only the primary outcome will be formally analysed using the generalised linear model described above. We designed the trial to have a non-binding futility bound with a one-sided *p* value of 0.3. The significance level will be used as the critical value for the *p* value of the observed treatment effect as this controls the type I error rate at the nominal level regardless of the true control event rate [45].

The measures to safeguard the confidentiality of the interim analysis results and minimise potential operational bias are detailed below:The independent DMC will receive a closed report prepared by the unblinded trial statistician showing the between-group differences of each intervention arm compared with TAU.If both intervention arms meet the criteria to continue in stage 2 (one-sided *p* value ≤ 0.3), no interim analysis results will be shared with the TMG or TSC, and the study will continue as three-arm trial, provided this is endorsed by the TSC on the recommendation of the DMC.If one or both interventions arms just exceeds the threshold for futility (one-sided *p* value > 0.3 and < 0.4), we will provide the DMC with additional information about the between-group differences on the CSSRS to guide a decision on whether one or both arms should continue in stage 2.If one intervention arm clearly exceeds the threshold for futility (one-sided *p* value ≥ 0.4), or if following the additional information on CSSRS the DMC recommends dropping one arm, the interim analysis results for this comparison only will be shared with the TMG and TSC on the recommendation of the DMC. This arm will be dropped from stage 2 of the study. The interim analysis results of the remaining arm will not be shared with the TMG or TSC.If both arms are recommended to be dropped, following confirmation of the recommendation of the TSC by the funder and sponsor, we will terminate recruitment to the study for lack-of-benefit in either arm.

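### The family-wise error rate of 0.0397 assumes that the stage 1 futility rule is always obeyed, but the protocol makes that rule non-binding; the non-binding maximum is about 0.047

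*Protocol article*

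**What the plan says.** The Sample size section gives the design levels: "One-sided significance levels of 30% and 2.5% and powers of 92% and 90% are used in the 1st and 2nd stages respectively". It then gives one overall error rate, without qualification, and a reason for not adjusting: "The overall family-wise error rate (FWER) is 0.0397. There is no need to account for multiple testing in a multi-arm trial with independent comparators". It also fixes the final one-sided alpha at 0.025.

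The Interim analyses section describes the stage 1 rule differently from what that rate needs: "We designed the trial to have a non-binding futility bound with a one-sided *p* value of 0.3". Three outcomes follow for an arm:

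- One-sided p of 0.3 or less: the arm meets the criterion to continue.
- p between 0.3 and 0.4: the DMC also receives CSSRS differences "to guide a decision on whether one or both arms should continue in stage 2".
- p of 0.4 or more: the arm is to be dropped.

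On the comparisons themselves, Sequence generation says "We use a 2:2:3 allocation in favour of TAU", and the Statistical methods section says "For each pairwise comparison with TAU, we will report the difference in proportion of admissions". There are thus two comparisons, PREVAIL and SAFETEL, each against the same TAU arm.

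**The concern.** An FWER for a two-stage design can be worked out in two ways. If arms that fail the futility rule always stop, some false positives that would have appeared at the final analysis are removed at stage 1, and the rate falls. If the rule is non-binding, arms may continue despite failing it, so that reduction cannot be counted on. The guaranteed rate must then come from the final test alone.

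The protocol calls the bound non-binding, yet its single FWER is the size expected under a binding rule, and the article does not say which basis was used. The DMC, weighing an arm in the 0.3 to 0.4 zone, and later readers of the results could take 0.0397 as a guarantee. It would no longer hold once the permitted discretion was used.

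**Working it through.** **Inputs, all from the protocol article**

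- One-sided levels 0.30 and 0.025 (Sample size), so the critical values are z = 0.524 and 1.960.
- Allocation 2:2:3 (Sequence generation). The ratio of an intervention arm to TAU is A = 2/3, so the between-arm correlation is A/(1 + A) = (2/3)/(5/3) = 0.40.
- Same outcome at both stages (Sample size), so the between-stage correlation for one arm is √t, where t is the information fraction. Across arms and stages it is 0.40 × √t.
- Interim at 385 participants with outcome data; maximum 1064 randomised; 5% loss. 1064 × 0.95 is about 1011 analysed.

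**Formulas, under the global null with multivariate normal test statistics**

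- Rule obeyed: P₁ = P(Z₁ > 0.524 and Z₂ > 1.960) for one arm, and P₁₂ = the probability that both arms pass both stages. FWER = 2P₁ − P₁₂.
- Rule ignored: FWER = 2 × 0.025 − P(both final statistics > 1.960). This does not depend on t.

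**Step 1: reproduce the plan's figure.** The article does not state t, so several values were tried, with stopping at p > 0.3 always obeyed.

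| Information fraction t | P₁ | P₁₂ | FWER |
|---|---|---|---|
| 385 × 0.95/1064 = 0.344 | 0.0211 | 0.0026 | 0.0397 |
| 0.354 (unpooled sample-size formula, 153.26/432.56 TAU participants) | 0.0213 | 0.0026 | 0.0400 |
| 385/1064 = 0.362 | 0.0214 | 0.0026 | 0.0403 |
| 385/1011 = 0.381 | 0.0218 | 0.0027 | 0.0409 |

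The FWER column is computed from unrounded terms. The stated value is recovered to four decimals at t = 0.344 and closely approached at the others.

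**Step 2: stop only at p ≥ 0.4.** This is the fullest use of the written DMC discretion, with stage 1 critical value z = 0.253. FWER is 0.0426 at t = 0.344, 0.0431 at t = 0.362 and 0.0435 at t = 0.381, so about 0.043.

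**Step 3: ignore futility.** P(both final statistics > 1.960) at correlation 0.40 is 0.00336. FWER = 0.0500 − 0.00336 = 0.0466. A simulation of 8 million draws also gave 0.0466.

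**Step 4: could 0.0397 be a non-binding value?** Only with a between-arm correlation of about 0.78. Allocation at 2:2:3 gives 0.40.

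**Size of the gap.** 0.0466 − 0.0397 = 0.0069. 0.0397/0.0466 = 0.85, so the stated figure is about 15% below the maximum. Against full use of the written discretion, the gap is 0.0426 − 0.0397 = 0.0029 to 0.0435 − 0.0397 = 0.0038.

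**The case against.** The strongest reply is that the written procedure does not allow 0.0466. Discretion ends at p = 0.4, and beyond that an arm is to be dropped. A reader might infer that the procedure as written carries a 4.7% error rate; it does not. Followed to the letter, it gives about 0.043 at most. The 0.0466 is the conventional maximum that goes with the label non-binding. This stands, and both figures need their basis stated. It does not rescue 0.0397, which is below even the 0.043.

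A second reply is that the origin of 0.0397 is inferred. That is fair. The exact match at t = 0.344 takes 5% loss off the 385, who are already counted as having outcome data, and the more natural 385/1011 gives 0.0409. But every plausible t puts the binding value near 0.040 to 0.041, and the non-binding value is the same at every t.

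Third, the figures are normal approximations. A binomial simulation with a 15% admission rate in all arms gave 0.0404 with the rule obeyed and 0.0457 with it ignored. The gap narrows but remains.

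Fourth, a reader might take the remark about independence as denying that TAU is shared. The document does not support that reading firmly: the phrase may mean distinct interventions answering separate questions, and the source cited for it is not available here. The wording is loose, but the point does not depend on it.

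Finally, nothing operational moves. That is correct, and it limits the severity.

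**Conclusion.** The point holds as a moderate correction. The unqualified 0.0397 belongs to a rule under which every arm with p > 0.3 stops, and the protocol describes a non-binding rule. The figure is about 0.043 if the DMC's written discretion is fully used, and at most 0.0466 if futility is ignored. These rest on the stated levels, 2:2:3 allocation throughout, a shared TAU arm and the normal approximation. The 0.0466 does not depend on the information fraction.

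A reader might go further and infer that error control has failed or that the trial is under-sized. The document does not support this. Each comparison is still tested at one-sided 0.025, which the protocol states. The maximum stays below 0.05 one-sided, no FWER target is set that could be breached, and the sample size reproduces: 433 + 2 × 289 = 1011, and 1011/0.95 is about 1064. Nor does the protocol claim a pairwise error of about 0.021; that is only what the binding calculation implies.

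**What to change.** In the Sample size section, report the maximum one-sided FWER with futility treated as non-binding, about 0.047, and keep 0.0397 only if it is labelled as conditional on stopping every arm with p > 0.3. Giving the information fraction behind 0.0397 would let a reader check it. The value of about 0.043 for full use of the 0.3 to 0.4 discretion could be added for the DMC.

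Replace the sentence about independence with a plain statement that the two comparisons share TAU (correlation 0.40 at 2:2:3), and that pairwise error is controlled at one-sided 0.025 by choice, without a multiplicity adjustment.

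The cost is wording in the protocol, carried into the analysis plan if it repeats the figure, and a slightly less favourable reported rate. No participants, critical values or power calculations change.

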### Recruitment

We use multiple methods to ensure our recruitment strategy has maximum engagement with the relevant clinical services. The initial approach to these services is typically made by the PIs through established links at the site and where required the PIs have engaged with the services to support and problem solve any challenges with recruitment. Each site has two RAs who are embedded within the crisis teams, with weekly/bi-weekly attendance at the service team meetings sustaining a study presence and facilitating participant identification. Furthermore, this approach builds a positive relationship between the clinical staff and research team. To ensure ongoing engagement, the research team provides educational presentations regarding the research, as well as a regular supply of study leaflets and posters to the crisis teams. We also provide regular updates through study newsletters. Our recruitment approach and presence within the crisis services ensures fair access to all potential participants throughout the lifetime of recruitment by ensuring the crisis teams have confidence in the study design and team. We work closely with the National Institute for Health and Care Research (NIHR) Clinical Research Network and NHS Research Scotland Mental Health Network. Where in place, we utilise local NHS Trust standard operating procedures (SOP) for delegation of screening and first contact from service staff to the RDT.

Eligible participants are identified by a clinician from their crisis team or another individual delegated responsibility to identify potential participants by the crisis team leader. The initial approach to introduce the study and ascertain if the patient wants to proceed to be referred to a member of the study team is made by the crisis team clinician or delegated by the crisis team leader to another individual responsible for first approach. Following receipt of a referral, the site RAs contact the potential participant to introduce the study, answer preliminary questions and should the potential participant wish to arrange an informed consent visit (ICV) they are sent the PIS ahead of the ICV with at least 24 h to consider the information.

## Assignment of interventions: allocation

### Sequence generation

Randomisation (at the individual level) is independent and concealed using randomised-permuted blocks of random size administered by the King’s Clinical Trials Unit (KCTU; UK Clinical Research Collaboration registration 053) and which are not known to the study team. Randomisation is stratified by site. We use a 2:2:3 allocation in favour of TAU. In stage 2, we will keep the existing allocation or switch to 1:1 allocation if there is only one active intervention arm.

### Concealment mechanism

Randomisation is implemented via a study-specific web-based portal developed by KCTU. On randomisation the allocation is made known to the interventionists, the trial managers to monitor adherence to the randomisation algorithm and assign interventions to cases, the PI to ensure site oversight and the Trial Administrator who is delegated the duty of posting the allocation letter. Blinding of the allocation code of a subject is maintained for RAs until all outcome measures for that participant have been collected. All staff are required to follow a standard operating procedure for maintaining concealment of allocation and report of any accidental unblindings of the allocation.

### Implementation

Following informed and written consent, eligible participants are randomised within 2 working days by RAs blind to allocation using the study-specific web-based portal developed by the KCTU.

## Assignment of interventions: blinding

### Who will be blinded

RAPID is a single-blind RCT and as such trial participants are not blinded to assignment, since this would be impossible given the nature of the psychosocial interventions. For ethical and clinical reasons, we do not withhold the outcome of allocation from care providers given trial participants are likely to experience regular suicidal crises and study interventionists are required to share with the care provider any risks to self or others reported. Our primary outcome is objective (admission to hospital (yes/no)), so should not be subject to rater bias. RAs are blind to treatment condition. Blindness is maintained using a wide range of measures set out in our SOP for blinding including separate offices for the PSWs and APs and RAs, protocols for reminding crisis team clinicians, participants and family members about the blind and data file security of randomisation information. Blind breaks are recorded by the Trial Manager and reviewed by the Chief Investigator for patterns. When a blind break does occur, where possible, we will identify an independent assessor with whom the blind has not been broken to complete subsequent follow-ups, subject to any threats to participant engagement with follow-up. The trial statistician will remain blind to treatment allocation until the SAP has been finalised and approved; the senior trial statistician will remain blind until all analyses have been completed. Interim analysis of the primary outcome (admissions) will be carried out by the unblinded trial statistician and checked by an independent blinded trial statistician. Final analyses will be carried out by the trial statistician and overseen by the senior trial statistician.

### Procedure for unblinding if needed

There are no conditions under which the blind will be purposively broken.

## Data collection and management

### Plans to promote participant retention and complete follow-up

Our primary outcome of admissions is collected from routine electronic patient records (EPR) and so we expect minimal missing data. At point of consent, potential participants are informed that should they wish to change their status in the study they can choose from a number of options that includes dropping out of the intervention only, dropping out of the intervention (if allocated) and/or the research assessments whilst continuing consent to the primary outcome data collection from the EPR, or withdraw from all aspects of the study including primary outcome data collection via the EPR. Should a participant choose to withdraw from all research procedures we will not collect any outcome data from the point of withdrawal but will retain the data we have collected to the point of withdrawal. The choice in change of status provides maximum opportunity to continue to collect the primary outcome data. We allow for a small amount of consent withdrawal and other factors at a conservative level of 5%.

For the secondary clinical measures, a 20% loss to follow-up is approaching the upper limit beyond which the validity of trial findings would be jeopardised. To best support our participants and promote retention to follow-up, the RAs are trained to work in a person-centred manner where the participant is given as much control as possible over the method for the assessment (in-person or remote), location including option for a home visit or in a community centre, and time and date of the assessment. If a potential participant is unable to participate due to lack of a telephone/mobile phone, then we provide them with a mobile phone and 6-month data package. For ethical reasons, if we provide a participant with a mobile phone, we will allow them to keep it after they exit the trial to prevent reinstating digital exclusion and digital poverty for those that required a phone. Data are collected at three time points: baseline, 3-month and 6-month assessments. We have carefully selected the research assessment time points to ensure we can address the research questions, whilst balancing this with minimising participant burden. The assessment measures are clearly prioritised so that the most important will be collected first to minimise missing data and manage participant burden. RAs follow a distress protocol; this includes the option of a telephone contact within two working days of the assessments to provide a space for structured space to feedback on the assessment process and ask any questions about the process that may have arisen after the meeting. Participants are compensated for their time per assessment with £10 in cash, voucher or bank transfer. These processes are consistent with systematic review evidence for increasing retention in clinical trials [44]. To ensure continued oversight and support for RAs with follow-up retention, the RAs received weekly trial management supervision that includes monitoring of follow-up rate retention and proactive problem-solving for issues with completing assessments.

### Data management

All participant data are pseudonymised using a unique trial identification number allocated at enrolment, with data always kept securely at NHS and University bases in accordance with the requirements of GDPR. Paper source data worksheets are completed at sites and transferred to a web-based electronic data capture system backed by an electronic data management system (InferMed MACRO version 4; KCTU) that is hosted on a dedicated server within KCTU. The system is compliant with Good Clinical Practice. Roles are assigned to users, giving the ability to enter data relating to participants or to view data and raise discrepancies. A full audit trail of data entry and any subsequent changes to entered data is automatically date and time stamped, alongside information about the user making the entry/changes within the system. No data is entered onto the system unless a participant has signed a consent form to participate in the trial. The system is programmed to perform validation checks, such as range checks to prevent data entry errors. Missing data codes are programmed into fields, for ease of analysis. The system is also programmed to flag up when a missing data code is entered, to aid monitoring. A standard feature of InferMed MACRO data entry system is the built-in audit trail on all data fields, the automatic saving of data as you leave a form, and the ability to maintain a record of ‘source data verification’ checks. No data are amended independently of the study site responsible for entering the data. Data entered from paper source worksheets completed at sites will be checked against the electronic data for accuracy. Accuracy will be checked for 100% of the primary outcome on the post-baseline time points across all sites. If the error rate is greater than 1%, accuracy checks for all data will be triggered.

